### Trial design

A randomized (1:1 allocation ratio) feasibility study design will be used. The protocol will be reported in accordance with the Standard Protocol Items: Recommendations for Interventional Trials (SPIRIT) [30] (for a checklist please see Additional file 1) and with further guidance from the Consolidated Standards of Reporting Trials (CONSORT) extension for randomized pilot and feasibility trials [31].

### Patient involvement

Patients and members of the public will be involved as research partners throughout the research process in accordance with Patient and Public Partnership guidelines [32]. During the preparation and feasibility phase one patient representative joined the steering group, was a coapplicant on the funding application, provided feedback on parts of the ethical application (summaries, patient information, and informed consent), and tested the usability of the accelerometer and related written instructions. The patient representative will be regularly updated on the status of the research process and informed via email communication once the feasibility trial has been published. After the feasibility study, additional patient representatives will be recruited to work together with the researchers during the process of finalizing the design of the full trial.

### Participants and study settings

Participants will be recruited from two private spine clinics with referrals from the regions, in Sweden: Capio Spine Center Göteborg and Ryggkirurgiskt centrum (RKC), Sophiahemmet, Stockholm. Inclusion criteria: (i) patients planned for decompression surgery (without concomitant fusion) due to lumbar central spinal stenosis; (ii) patients > 18 years of age. Exclusion criteria: (i) patients with malignancy, severe neurological -or rheumatological disease, idiopathic scoliosis, or isthmic spondylolisthesis; (ii) persons unable to understand written information and communicate in Swedish; and (iii) patients with untreated/unstable heart disease that prohibits physical capacity tests. For patients meeting the inclusion criteria, the following screening criteria should also be fulfilled: (i) low level of physical activity (i.e. persons who do not meet WHO’s physical activity recommendations of a weekly minimum of 150 min of physical activity of moderate intensity), and (ii) higher levels of fear of movement or pain catastrophizing, equivalent with scores ≥ 37 on the Tampa Scale of Kinesiophobia (TSK) [33] and ≥ 30 on the Pain Catastrophizing Scale (PCS) [34].

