**Methods:**

Thirty patients planned for decompression surgery due to central lumbar spinal stenosis who present with low physical activity, pain catastrophizing or fear of movement, will be included in a randomized feasibility study. All patients will be randomly allocated to either Get Back_feasibility_ or usual physical therapy. Get Back_feasibility_ aims to increase the patient’s physical activity level by combining a person-centred and cognitive behavioural approach. It comprises 10 video and telephone sessions led by a physical therapist over 12 weeks (pre/postoperatively). Outcomes are treatment fidelity (treatment dose, adherence, and content), process feasibility (recruitment, intervention use, and acceptability of measurements and intervention), and variables related to the intervention content (steps per day, physical activity level, pain catastrophizing, fear of movement, and general self-efficacy). Treatment fidelity and feasibility data will be assessed during the full study period (12 weeks). Physical activity, physical capacity, and patient-reported outcomes will be assessed digitally at baseline (2 weeks preoperatively) and 11–12 weeks postoperatively. Variables related to the intervention content will be monitored weekly through a digital application. Feasibility data will be analysed descriptively and inferentially using a nonparametric approach, data from repeated measures will be displayed graphically and data from telephone interviews will be analysed using content analysis with a descriptive manifest approach.

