**Discussion:**

The results will provide information on whether Get Back in its present format is feasible and can be evaluated for effectiveness in a larger randomized controlled trial, for patients with a low physical activity level and a high fear of movement who are undergoing decompression surgery.

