## Methods

### Research questions

All research questions below are formulated in the PICO format and concern patients with a low physical activity level and high pain-related catastrophizing and/or fear of movement receiving decompression surgery for lumbar spinal stenosis.

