### Recruitment

All patients will have a consultation with a spine surgery specialist who based on anamnesis and clinical and radiological findings will determine the diagnosis and give recommendations regarding the treatment regime(s). Patients planned for surgery and eligible for the study will be identified by an independent local recruiter who will contact the patients by phone, provide oral study information and screen for risk factors. The independent recruiter will also ascertain whether the participant has the required technology (smartphone, computer, or tablet with a camera, as well as an internet or mobile network connection). If the screening criteria are fulfilled, the patient will be asked for participation and oral informed consent. A digital baseline assessment will be scheduled with an independent observer (physical therapist) approximately 2 weeks before surgery. Before the baseline assessment, written informed consent will be obtained digitally. An overview of the study flow is seen in Fig. 1.

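### Screening criterion (ii) joins its two constructs with *or* but its two cut-offs with *and*, so the rule that decides enrolment and the RQ5 eligibility percentage contradicts itself

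*Protocol article*

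**What the plan says.** The entry rule appears in several places in the protocol article.

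- **Participants and study settings** is the only place with cut-offs. It states that "the following screening criteria should also be fulfilled: (i) low level of physical activity" and then, as (ii), "higher levels of fear of movement or pain catastrophizing, equivalent with scores" of "≥ 37 on the Tampa Scale of Kinesiophobia (TSK) [33] and ≥ 30 on the Pain Catastrophizing Scale (PCS". Items (i) and (ii) are joined by *and*.
- **Background, last paragraph (objective)** describes low activity together with catastrophizing *or* fear of movement.
- **Research questions** says that all the questions "concern patients with a low physical activity level and high pain-related catastrophizing and/or fear of movement".
- **Abstract, Methods** describes patients "who present with low physical activity, pain catastrophizing or fear of movement, will be included in a randomized feasibility study".
- **Abstract, Discussion** looks ahead to a larger trial "for patients with a low physical activity level and a high fear of movement who are undergoing decompression surgery".

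Under Recruitment, a local recruiter screens by phone, and only patients who meet the screening criteria are invited. Research question 5 (RQ5) asks what percentage of patients meeting the inclusion criteria are eligible after screening. Process and resource feasibility lists the same percentage as a recruitment outcome.

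**The concern.** A criterion with numerical cut-offs is normally applied through its numbers. Here the numbers, as joined, require both scales to be high, while the words introducing them require only one. A recruiter who follows the words and a recruiter who follows the numbers would decide differently about any patient who is high on one scale only.

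Two things depend on this. The first is who is enrolled: the both-scales rule selects a narrower group, with every patient high on fear and on catastrophizing. The second is RQ5, whose numerator is defined by this rule. The Discussion says the intervention and study procedure will be refined from these results before a full randomized trial. An eligibility percentage cannot inform that step unless the rule behind it is known.

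This is not detail that an article may leave to a fuller document. The article states the rule, and states it two ways.

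**Working it through.** **Step 1. The statements side by side.** Write L for low activity, T for TSK ≥ 37 and C for PCS ≥ 30 (or, where no cut-off is given, the matching construct).

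| Place | Rule as worded |
|---|---|
| Participants and study settings, constructs | L and (T or C) |
| Participants and study settings, cut-offs | L and (T and C) |
| Background, objective | L and (C or T) |
| Research questions | L and (C and/or T) |
| Abstract, Methods | L, C or T (a list) |
| Abstract, Discussion | L and T |

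Inclusive *or* and *and/or* are the same rule, so rows 1, 3 and 4 agree. Row 2 contradicts them. Row 5 is a condensed summary, and row 6 describes a possible future trial. Neither is an operating criterion.

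**Step 2. There is no figure to reproduce.** The article gives no expected eligibility percentage, no prevalence for either scale and no number to be screened. The target of 30 comes from a literature minimum of 24 plus a margin for withdrawals, so it does not depend on the criterion.

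**Step 3. Size among low-active patients, on assumed inputs.** Let p_T and p_C be the proportions of low-active patients at or above each cut-off, and r the correlation of two underlying standard normal variables. None of these is in the documents. Assumed ranges: p_T 0.40–0.60, p_C 0.15–0.30, r 0.3–0.6.

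- Both scales: P(T and C) = Φ₂(z(p_T), z(p_C); r), where Φ₂ is the bivariate normal distribution function and z the normal quantile.
- Either scale: P(T or C) = p_T + p_C − P(T and C).

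| p_T | p_C | r | Both | Either | Either ÷ both |
|---|---|---|---|---|---|
| 0.40 | 0.15 | 0.3 | 0.088 | 0.40 + 0.15 − 0.088 = 0.462 | 5.2 |
| 0.40 | 0.15 | 0.6 | 0.118 | 0.432 | 3.6 |
| 0.40 | 0.30 | 0.6 | 0.209 | 0.491 | 2.4 |
| 0.60 | 0.15 | 0.3 | 0.116 | 0.634 | 5.5 |
| 0.60 | 0.30 | 0.3 | 0.220 | 0.680 | 3.1 |
| 0.60 | 0.30 | 0.6 | 0.260 | 0.640 | 2.5 |

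Over the whole range, both scales gives 8.8–26.0%, either scale gives 43.2–68.0%, and the ratio runs from 2.4 to 5.5.

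**Step 4. From low-active patients to RQ5.** The percentages in Step 3 are conditional on low activity. RQ5's denominator is all patients meeting the inclusion criteria, so each must be multiplied by the proportion with low activity. That factor is common to both rules and cancels from the ratio. With wider assumptions (low activity 50–80% and independent of both scales, p_T 30–60%, p_C 15–35%, r 0.3–0.6), the RQ5 percentage is about 4–24% for both scales and 17–56% for either, again roughly a 2- to 5-fold difference. One case within that range, with low activity 50%, p_T 50%, p_C 25% and r 0.6:

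- both scales: 10.2%, so about 30 ÷ 0.102 ≈ 295 patients screened to find 30 eligible;
- either scale: 27.3%, so about 30 ÷ 0.273 ≈ 110.

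**The case against.** The strongest reply is that the article already points to one reading. The objective, the research questions and the opening words of criterion (ii) all say either construct. The later *and* can be taken as listing one cut-off for each construct just named, in the sense of *respectively*. On the both-scales reading, the *or* in the same sentence would do nothing. This stands as an account of likely intent and is why the severity is moderate. It does not remove the contradiction, because the sentence holding the cut-offs does not say *respectively* and its numbers as joined require both.

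A reader might go further in four ways that the documents do not support.

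- **Any one of three features suffices.** The list in the abstract's Methods can be read so, but the numbered (i) *and* (ii) in the main text makes low activity compulsory. The abstract's Discussion, which names fear alone, is not an eligibility statement. Both are matters of abstract wording.
- **The two sites have used different rules, so a pooled figure is meaningless.** Nothing shows this. The recruiters' own screening materials are not in the article. The text permits divergence; it does not show it.
- **The technology check leaves eligibility undefined.** The Recruitment section discloses it: "The independent recruiter will also ascertain whether the participant has the required technology", with the devices and connection listed. Whether lacking them counts as a screening failure is a reporting detail.
- **RQ5 is the decisive result.** It is one of eleven questions, and the article ties no progression threshold to it.

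It is also fair to object that the percentages in the working rest on assumed prevalences. They do, and they are offered only to show that the choice of connector is not trivial.

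**Conclusion.** The concern holds as an internal contradiction in one operative sentence: criterion (ii) uses *or* for the constructs and *and* for the cut-offs, and the literal cut-off rule conflicts with the objective and the research questions. It bears on who is invited and on the RQ5 percentage.

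The either-scale rule would admit about 2.4 to 5.5 times as many low-active patients as the both-scales rule. That range rests wholly on the assumed prevalences, the assumed correlation and the bivariate normal model. The conditional percentages behind it are not themselves RQ5 percentages.

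The change should be made, but it is not critical. The likely intent can be recovered from the rest of the article, the sample size is untouched, and no misapplication has been shown. Confidence is high on the wording and limited on the size of the consequence.

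**What to change.** - Rewrite criterion (ii) under Participants and study settings as one Boolean rule with the cut-offs inside it. The rule consistent with the objective and the research questions is low activity AND (TSK ≥ 37 OR PCS ≥ 30). If the investigators meant both scales, they should say so and change those two sections instead.
- Bring the abstract's Methods and Discussion wording into line with that rule.
- Confirm in writing which rule each of the two sites has applied since enrolment began on 17 April 2023.
- Report RQ5 with the rule stated beside the percentage. If the sites turn out to have differed, report the percentage by site. As a minor addition, say whether patients lacking the required technology are counted as ineligible.

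The cost is a few words of protocol text, a note to the recruiters and a check of whatever screening records the sites hold. Sample size, randomization and outcome measures do not change.

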### Recruitment

All patients will have a consultation with a spine surgery specialist who based on anamnesis and clinical and radiological findings will determine the diagnosis and give recommendations regarding the treatment regime(s). Patients planned for surgery and eligible for the study will be identified by an independent local recruiter who will contact the patients by phone, provide oral study information and screen for risk factors. The independent recruiter will also ascertain whether the participant has the required technology (smartphone, computer, or tablet with a camera, as well as an internet or mobile network connection). If the screening criteria are fulfilled, the patient will be asked for participation and oral informed consent. A digital baseline assessment will be scheduled with an independent observer (physical therapist) approximately 2 weeks before surgery. Before the baseline assessment, written informed consent will be obtained digitally. An overview of the study flow is seen in Fig. 1.

**Fig. 1 Fig1:**
[figure not shown]
Study flow including allocation, treatment, and follow-up phases

### Randomization

A statistician will generate one computerized list per recruitment site with the random allocation sequence. A person not involved in either recruitment or data collection will administer the lists into concealed envelopes. The concealed and numbered envelopes will be consecutively opened by a study coordinator after each patient’s baseline assessment and allocate the patients to either Get Back_feasibility_ (*n* = 15) or usual physical therapy (*n* = 15). The independent observer will be blinded to the group allocation. Participants allocated to the intervention will not participate in physical therapy at the operating clinic from postoperative discharge and as long as the Get Back intervention is conducted (approximately 10–11 weeks).

### Theoretical framework of the intervention

Get Back combines a person-centred philosophical standpoint [35, 36] with a behavioural medicine perspective [37] on pre- and rehabilitation. The overall aim is to improve physical activity as a core indicator for health. Physical activity should be promoted for patients with chronic pain as well as for patients with disorders affecting mobility in combination with pain, such as spinal stenosis patients. First, physical activity decreases the risk for noncommunicable diseases and thereby decreases the risk for premature death and years lived with disability [38]. Second, physical activity has a hypoalgesic effect [39].

PCC, as defined by the framework developed by the University of Gothenburg Centre for Person-Centred Care (GPCC) [35], is an approach based on ethical principles that aims to involve patients as active partners in their care and treatment and establish a partnership reflecting the expertise of both the patient and health professionals [35, 36]. The core component of PCC is the cocreation of care through partnership between patients, their families and informal carers, and health professionals. Since 2010 the GPCC framework has been operationalized and evaluated in several controlled trials [40] and implemented in clinical practice based on three routines. These routines are based on listening to the patient’s narrative to identify personal needs and resources, together with medical status, to initiate a partnership; working the partnership to achieve commonly agreed goals; and safeguarding the partnership by documenting a jointly agreed health plan. Within other research fields, e.g. in patients recovering from acute coronary syndrome and patients with common mental disorders, it has been indicated that person-centred care increases self-efficacy regarding symptom control respectively in general [26, 41].

The treatment content is developed based on learning theory and, specifically, the fear-avoidance model of pain [33, 42]. In short, the model explains how, depending on the threat interpretation of pain, a person can either prioritize avoiding activities that could further elicit the pain or prioritize valued life goals and behaviours leading to recovery. Exposure aims to tackle avoidance behaviour to improve functioning through increased approach behaviour, not fear-reduction per se [43]. Pain communication (pain neuroscience education, PNE) aims to reconceptualize and undermine the threat value of an individual’s pain experience [44]. In Get Back_feasibility_, pain communication is conceptualized as a prerequisite to an active exposure approach to physical activity and not an independent intervention.

### Intervention content and procedure

Get Back_feasibility_ will be delivered by a physical therapist (Study PT) via video and telephone, enabling patients to access the intervention from their homes. Video communication will be conducted on the Doctrin platform (provided by Doctrin AB), which is an approved medical device, and all data will be processed according to the Swedish Patient Data Act and the EU Data Protection Regulation (GDPR). Get Back_feasibility_ includes five treatment sessions with predefined aims and content delivered through videocall (core sessions) and five shorter reinforcing telephone sessions (booster sessions). Each core session will last for approximately 1 h, and each booster session will last < 30 min. Out-of-session tasks [45] will be formulated at every session and followed up at the next. The intervention will span over 12 weeks (1 week preoperatively until 11 weeks postoperatively). The Study PT will have experience and education in PCC and pain. All parts of the intervention are based on a person-centred approach and are theoretically based on the modified version of the fear-avoidance model [27, 42]. Should unexpected findings of a medical nature be observed during any of the sessions with the study physical therapist, these will be discussed with medical experts in the research group. The sessions and included Behavioural Change Techniques (BCTs) according to the BCT taxonomy [46] are described below and illustrated in Fig. 2.

**Fig. 2 Fig2:**
[figure not shown]
An overall schematic illustration of the intervention (Get Back_feasibility_)

#### Preparation phase—initiating and safeguarding partnership

*Core session 1: Person-centred analysis and treatment start-up (1 week preoperatively)*

The focus of the first core session is to engage the patient as an active, equal partner in the treatment and to formulate a shared health plan according to PCC [35]. The health plan will be based on the results from baseline measurements and on actively listening to the patient’s narrative. Using person-centred communication (e.g. active listening, open-ended questions) [47] and the modified fear-avoidance model as tools, the focus will be on identifying the persons’ unique resources, needs and challenges for engaging in physical activity. The shared health plan will further include reasonable and reachable goals, both personally valued long-term physical activity outcomes and more short-term everyday activity goals, as well as strategies and specific exercises needed to reach each goal.

Examples of out-of-session tasks:Self-monitoring [45] steps per day as a behaviour reinforcement tool [48, 49].Reading information material in preparation for session 2 [50].

*BCTs include* goal setting (behaviour and outcome) (1.1, 1.3), action planning (1.4), feedback on behaviour (2.2), and self-monitoring of behaviour (2.3).

*Core session 2: Person-centred preoperative communication (1 week preoperatively)*

The focus of core session 2 is to undermine the threat value of postoperative pain and early physical activity by cocreating increased knowledge about pain, physical activity, and fear-avoidance factors [51]. The structure of the session will be based on recommendations by Goudman et al. [52] and tailored to fit the patient’s own preferences and questions arising from session 1, in line with PCC. The evidence-base for Get Back will be discussed: Healthy physical activity behaviour post-surgery can improve recovery and improve health and quality of life. Moreover, that postoperative pain is normal, expected and not an accurate reflection of the result of surgery. The Study PT will ensure the patient that the recommended physical activity will be in line with potential individual postoperative recommendations. The health plan will be revisited and documented. The PT will follow up on the activity-tracker, give reinforcing feedback on the behaviour and engage in problem solving if needed.

Examples of out-of-session tasks:Self-monitoring [45] steps per day as a behaviour reinforcement tool [48, 49].

*BCTs include* action planning (1.4), feedback on behaviour (2.2), self-monitoring of behaviour (2.3), information about health consequences (5.1), and instructions on how to perform a behaviour (4.1).

#### Behavioural activation phase—working and safeguarding partnership

*Core session 3: Person-centred postoperative analysis and activity initiation (1 week postoperatively)*

The focus of this core session is to detect barriers for early postoperative physical activity and help the patient to gradually start increasing physical activity behaviours after surgery. The preoperative pain- and physical activity communication from session 2 will be followed up based on the patients’ current thoughts and coping strategies related to postoperative pain and movement [52]. Behaviour analysis, using the fear-avoidance model as an exemplifying tool, will be used to cocreate an understanding of the patient’s postoperative physical activity behaviour and its consequences. Then, in partnership, the patient and PT will plan for a graded increase in physical activity using self-monitoring and out-of-session tasks [45]. As walking is the recommended activity directly post-surgery, the focus will be on walking and increasing the number of steps per day. The patient’s own activity goals will be incorporated in the planning. All recommendations on early postoperative physical activity will be in line with individual postoperative regime made by the surgeon. The health plan, including personal goals, will be revisited and revised if needed.

Examples of out-of-session tasks:Behavioural experiment—the patient will be encouraged to test a planned increase in physical activity behaviour, along with preformulated hypotheses about the consequences and collection of data for the results to be analysed in session 4.Self-monitoring [45] steps per day as a behaviour reinforcement tool [48, 49].

*BCTs include* action planning (1,4), review of behaviour goals (1.5), behavioural experiments (4.4), graded tasks (8.7), exposure (7.7), behavioural rehearsal/practice (8.1), and self-monitoring of behaviour (2.3).

*Core session 4 + Booster sessions 1–3: Reinforcing physical activity (3–6 weeks postoperatively)*

The focus of this core session is to help the patient to further confront fear-avoidance beliefs related to increased physical activity behaviour and to undermine avoidance behaviour in relation to physical activity**.** The patient and PT will revisit the patient’s experience of being physically active in terms of thoughts, feelings, and short- and long-term consequences of a given behaviour. The PT will provide reinforcing feedback on self-monitoring physical activity behaviour and progress on daily activity goals. Behavioural analysis will be performed using the fear-avoidance model as an exemplifying tool to increase a shared understanding of the patients’ physical activity behaviour and related thoughts and consequences. The short- and long-term consequences of approach or avoidance behaviour will be discussed in relation to the persons’ long-term values in relation to physical activity. In partnership, the patient and PT will then plan for the patient to systematically confront fears and/or other potential barriers with the aim of decreasing avoidance and increasing approach behaviour related to physical activity (exposure) [43]. The Study PT will offer to be on the phone with the patient during the exposure as a facilitating factor. The health plan will be revisited and revised if needed. Depending on whether the patient reaches the set goals or experiences setbacks, new goal setting will be adapted for each patient’s situation.

Examples of out-of-session tasks:Exposure for avoidance behaviour related to physical activity.Self-monitoring [45] steps per day as a behaviour reinforcement tool [48, 49].

*BCTs include* a review of behaviour goals (1.5), self-monitoring of behaviour (2.3), behavioural experiments (4.4), exposure (7.7), behavioural rehearsal/practice (8.1), and graded tasks (8.7).

